**Vulnerable Populations**

No vulnerable populations are included in the research study.

**Populations Vulnerable to Undue Influence or Coercion**

We are not specifically targeting any vulnerable populations.

**Subject Recruitment**

900 potentially eligible subjects will be identified via a data abstraction by Penn Data Store using a data query algorithm that identifies patients who meet the inclusion criteria. Chart review will be conducted

to source 423 eligible participants from this pool of subjects.

## **Subject Compensation**

Participants will not be financially compensated for their participation.

## **Procedures**

**Screening - Phase 1:** We will submit a data request of patients from the CCA practices of University City and Valley Forge from the Penn DataStore, based on an EMR algorithm that determines guideline-concordant colorectal cancer screening within PennChart. We estimate approximately 900 screen-eligible patients will be identified through this EMR query, 423 of whom will be enrolled and randomized into the three arms. We anticipate conducting chart reviews for two months. During these chart reviews, the Research Assistants and the Research Coordinator will review the electronic medical record charts in PennChart (EPIC) to review each of the eligible patients pulled from Penn Data Store to confirm study eligibility.

**Randomization - Phase 2:** Subjects will be randomly assigned Study ID numbers and then randomized with stratification to one of three arms using a computer-generated randomization algorithm. The research coordinator will record the randomization assignments on a master list which will be maintained by the research coordinator on a password protected computer in a locked office. The research coordinator and research assistants will assemble the mailings based on this master list.

**Outreach & Follow-up - Phase 3:** Initial outreach letters will be sent to subjects. In the control arm the outreach will include a phone number to the VIP colonoscopy scheduling center. For the sequential choice arm, subjects will receive the same message as those in the control arm, indicating they are overdue for screening and including a phone number to the VIP screening scheduling center. For the active choice arm, subjects will receive both a mailed FIT kit and the option to call and schedule colonoscopy at the same time. After four weeks, a reminder letter will be sent to all subjects in all three arms who did not either schedule a colonoscopy appointment or complete and return a FIT kit. Subjects in the Control arm will receive a reminder letter that includes the same phone number to schedule colonoscopy. Subjects in the sequential choice arm will receive a second letter containing the phone number to the VIP screening scheduling center as well as a FIT kit. The active choice arm will receive a reminder that includes both the phone number to the VIP screening scheduling center and a reminder that they may alternatively complete the FIT that was initially mailed. The Research Coordinator and Research Assistants will be responsible for assembling the mailings. FIT kits will include a tube in which to deposit the stool sample, directions on how to collect and mail the sample, a letter about CRC screening, a lab requisition form, and a pre-paid return envelope.

**Sub-sample Questionnaire - Phase 5:**

A random subsample of 90 subjects will be selected to complete a questionnaire at least 4 **approximately 6 months** after they received the mailing. Through this questionnaire, ~~the subjects will~~ **be asked to explain their experience with CRC screening outreach. Additional questions will probe for potential barriers to screening participation, and ways to improve participation in the future.** ~~confirm their eligibility (e.g. that they had not had CRC screening within the USPSTF CRC screening guidelines) and provide additional demographic and socioeconomic status information as well as qualitative experience with the outreach materials and approach so that we can better understand what~~

populations, if any, may be more likely impacted by different types of outreach modalities when engaging in CRC screening. We anticipate these questionnaires to take 10 minutes to complete over the phone. The research staff will make no more than three attempts to speak directly with the subject.

## **Analysis Plan**

### **1.1 Power and Sample Size**

Approximately 900 potentially eligible subjects will be identified via a data abstraction by Penn Data Store. Through other projects in primary care practices at Penn Medicine we found the accuracy rate of the EMR algorithm to be approximately 75%. As such, we anticipate we will have enough patients to enroll 423 subjects (and randomize 141 into each arm). We estimate a base return rate for the colonoscopy only (control) arm to be 5%, and we will consider a meaningful increase in response rate to be ~~10~~ **11** percentage points for both the sequential choice and active choice arms as compared to control. This will be sufficient sample size to detect a ~~10~~ **11** percentage point increase in response rate using a two-tailed chi-square test with 80% power and a **Type 1 error rate of .025, accounting for two pairwise comparisons with Bonferroni correction ( $.05/2 = .025$ )**. ~~5% level of significance.~~

### **1.2 Data analysis**

The primary outcome is CRC screening completion (FIT or colonoscopy) within 4 months of initial outreach. We will conduct a chi-square analysis using Stata to compare arms 2 and 3 to arm 1 separately using intent-to-treat protocol. We will also compare arms 2 and 3 as a secondary analysis. We will quantitatively analyze the choice of screening test and evaluate the survey results by study arm. As exploratory analyses, we will evaluate response by practice location, age, gender, race/ethnicity, and income at the level of zip code.

Analysis will be conducted by blinded members of the research team at least four months after the last FIT is mailed.

## **Data Confidentiality**

Paper-based records will be kept in a secure location and only be accessible to personnel involved in the study. Computer-based files will only be made available to personnel involved in the study through the use of access privileges and passwords. Prior to access to any study- related information, personnel will be required to sign statements agreeing to protect the security and confidentiality of identifiable information. Wherever feasible, identifiers will be removed from study-related information. Precautions are in place to ensure the data is secure by using passwords and encryption, because the research involves web-based surveys.

## **Subject Confidentiality**

Information about study subjects will be kept confidential and managed according to the requirements of the Health Insurance Portability and Accountability Act of 1996 (HIPAA). All PHI will be maintained on UPHS servers. Source documents are maintained in PennChart. No source documents will be printed or maintained in paper form at the study site. Data from PennChart will be recorded in Penn Medicine's REDCap system. The investigator and study team (which includes the research coordinator, and research assistants) will have access to PHI within PennChart and REDCap. We will label all PHI within REDCap as identifiable information so that de-identified exports are possible. All reports that include identifiable information will be stored on the Innovation Center secure drive,

maintained behind the UPHS firewall. Once data analysis and manuscripts have been published, the databases will be removed from REDCap and the data will be de-identified on the secure drive. This deidentified dataset will be stored for up to five years after analysis is complete and manuscripts have been published. Once analysis is completed and any manuscripts are published, we will retain PHI no longer than seven years in accordance with government regulations, applicable policies, and institutional requirements.

#### **Database Security/Protection Against Risk**

To assure that patient, physician and other informant confidentiality is preserved, individual identifiers (such as name and medical record number/physician billing identifier) are stored in a single password protected system that is accessible only to study research, analysis and IT staff. This system is hosted on site at The University of Pennsylvania (UPenn) and is protected by a secure firewall. Once a participant is in this system, they will be given a unique study identification number (ID). Any datasets and computer files that leave the firewall will be stripped of all identifiers and individuals will be referred to by their study ID. The study ID will also be used on all analytical files.

The initial patient information collected for screening and recruitment will consist of name, address, phone number, dates, medical records numbers and health plan account numbers. This information will come from Electronic Chart reviews.

#### **Sensitive Research Information**

This Research does not involve collection of sensitive information about the subjects that should be excluded from the electronic medical record.

#### **Subject Privacy**

We will only interact with the subsample of subjects with which we plan to call to conduct a follow-up questionnaire. With these subjects, we will conduct phone calls in a private area. When we call subjects, we will confirm the identify before administering the questionnaire. We will not be interacting with subjects in person.

#### **Data Disclosure**

FIT test results will be disclosed to the subject's primary care physician for continuity of care.

#### **Protected Health Information/Data Protection**

- Name
- Street address, city, county, precinct, zip code, and equivalent geocodes
- All elements of dates (except year) for dates directly related to an individual and all ages over 89
- Telephone and fax numbers
- Electronic mail addresses
- Medical record numbers
- Health Plan ID numbers

## **Consent Process**

### 1.1 Overview

Waiver of consent for the main portion of this pilot study is being requested, as this study involves no more than minimal risk to subjects. Please see below. Verbal consent will be obtained from the subsample with whom we plan to conduct post intervention interviews (see script).

### 1.2 Children and Adolescents

Not applicable

### 1.3 Adult Subjects Not Competent to Give Consent

Waiver of consent is being requested.

## **Waiver of Consent**

### 1.1 Minimal Risk

This study involves no more than minimal risk to subjects. Colonoscopy and FIT are clinically available and utilized tests used to screen for colorectal cancer. The outreach methods in the three arms are all offered during routine clinical care either at Penn Medicine or other health systems across the country. The only research related activity is the randomization of subjects to different outreach strategies that would typically occur in practice.

### 1.2 Impact on Subjects Rights and Welfare

Subjects rights and welfare will not be adversely affected by the waiver of authorization and consent. All subjects will have the opportunity to voluntarily participate in CRC screening. Arm 1 (Colonoscopy only) will receive screening by colonoscopy if they elect. Arm 2 (Sequential Choice) will receive CRC screening either by Colonoscopy or FIT if they elect. Arm 3 (Active Choice) will receive CRC screening either by Colonoscopy or FIT if they elect. Each arm has the opportunity to engage in CRC screening through routine care as well.

### 1.3 Waiver Essential to Research

We believe that we would not be able to practically conduct the research without waiver of consent. If we had to obtain either written or verbal consent ahead of time, it would substantially limit our study population and it may alter their participation in the intervention. Thus, we would only learn about the response rate for patients who we were able to speak to for consent. This, would limit the generalizability to practice. Obtaining waiver of consent would allow us to avoid the potential selection/volunteer bias for inclusion of patients particularly interested in screening that can occur when consent is required. Since our main objective is to understand the potential influence varying outreach strategies on subject behavior, we believe that obtaining consent would compromise our primary objective. Additionally, we have received waiver of consent for similar studies related to colorectal cancer screening outreach.

### 1.4 Additional Information to Subjects

Subjects will receive information about the risks and benefits of FIT through our outreach and about the risk and benefits of colonoscopy from the physician performing the procedure.

#### 1.5 Written Statement of Research

No statement of research will be provided.

#### **Potential Study Risks**

The risks associated with this study are no more than minimal. There is the potential risk of breach of confidentiality. We will minimize this risk by using de-identified information whenever possible and by maintaining all identifiable information on a secure drive and/or in a HIPAA-compliant system (e.g. REDCap). There is also the risk of psychological harm associated with being screened for cancer. We will minimize this risk by communicating the results of the screening test to the subject in a timely fashion and facilitating the scheduling of diagnostic testing if the screening test is positive (as is usual practice for screening outreach programs).

#### **Potential Study Benefits**

If a participant completes colonoscopy or completes and returns the FIT, both of which are standard clinical care, the subjects will potentially benefit from participation by increasing the chances of identifying colorectal cancer at an early stage. Information learned from this study may benefit society through a better understanding of how to effectively increase overall participation rates in CRC screening which could in turn reduce the rate of CRC mortality.

#### **Data and Safety Monitoring**

Safety will be monitored on an ongoing basis by the PI and the study team. The PI or designee will review the study charts to evaluate events at each subject interaction to ensure the grade, relationship to the study procedure, expectedness and the course of action for each subject is documented.

#### **Risk/Benefit Assessment**

The risks associated with this study are no more than minimal. Better knowledge of how to increase mailed screening could potentially address one of the major barriers of accessing care, i.e. having patients come in for clinical office visits. Additionally, FIT is less invasive than colonoscopy and, according to the USPSTF, considered equally effective if conducted once a year (as opposed to having a colonoscopy once every ten years). For these reasons and those outlined in the above benefits section, the Principal Investigator believes that the risks of participating in the study are outweighed by the potential benefits of participating in the study.

## Summary of Protocol Changes Modifications LOG

977  
978

979 **Protocol:** Choice Architecture and Colorectal Cancer Screening Outreach

980 **University of Pennsylvania Principal Investigator:** [name]

981

| Date of Submission | Description of Modification                                                                                   | Rationale for Modification                                                                                                                                                                                                                                                                                                                                                                           | Approval date |
|--------------------|---------------------------------------------------------------------------------------------------------------|------------------------------------------------------------------------------------------------------------------------------------------------------------------------------------------------------------------------------------------------------------------------------------------------------------------------------------------------------------------------------------------------------|---------------|
| 06/28/2017         | Initial submission                                                                                            |                                                                                                                                                                                                                                                                                                                                                                                                      | 07/28/2017    |
| 09/06/2017         | Updates to study personnel                                                                                    | Add Research Assistant: [name]                                                                                                                                                                                                                                                                                                                                                               | 09/13/2017    |
| 11/21/2017         | Updates to study personnel                                                                                    | Add student Research Assistant: [name]
Remove student research assistant: [name]                                                                                                                                                                                                                                                                                                           | 11/29/2017    |
| 02/06/2018         | 1) Updates to study personnel
2) Updated patient materials (questionnaire)                                 | 1) Remove student research assistant: [name]
2) modified questionnaire to be more open ended, to gather more information and be more hypothesis generating than specific                                                                                                                                                                                                                       | 02/12/2018    |
| 04/27/2018         | 1) Updated patient materials (questionnaire)
2) Updated study protocol (Phase 5: Sub-sample Questionnaire) | Revised the questionnaire to be more of a guided interview with open ended questions to gather a broader set of experiences, aimed at informing further research opportunities.                                                                                                                                                                                                                      | 05/07/2018    |
| 05/16/2018         | 1) Updates to study personnel
2) Updated study protocol
3) Updated study protocol: analysis plan        | 1) Remove student research assistant: [name]; Remove study contact [name]; Add student research assistant: [name]
2) Updated format to study protocol to reflect original and all modifications
3) Before beginning any analysis, we felt it necessary to revisit outcomes and provide a more detailed/thorough analysis plan to ensure both were as complete as possible. | 05/16/2018    |
| 06/18/2018         | 1) Update study personnel
2) Continuing Review                                                             | 1) Add student intern: [name]                                                                                                                                                                                                                                                                                                                                                                  | 07/27/2018    |

982  
983

## Initial Statistical Analysis Plan

### **Analysis Plan**

#### 1.1 Power and Sample Size

Approximately 900 potentially eligible subjects will be identified via a data abstraction by Penn Data Store. Through other projects in primary care practices at Penn Medicine we found the accuracy rate of the EMR algorithm to be approximately 75%. As such, we anticipate we will have enough patients to enroll 423 subjects (and randomize 141 into each arm). We estimate a base return rate for the colonoscopy only (control) arm to be 5%, and we will consider a meaningful increase in response rate to be 10 percentage points for both the sequential choice and active choice arms as compared to control. This will be sufficient sample size to detect a 10 percentage point increase in response rate using a two-tailed chi-square test with 80% power and a 5% level of significance.

#### 1.2. Data Analysis

The primary outcome is CRC screening completion (FIT or colonoscopy) within 4 months of initial outreach. We will conduct a chi-square analysis using Stata to compare arms 2 and 3 to arm 1 separately using intent-to-treat protocol. We will also compare arms 2 and 3 as a secondary analysis. We will quantitatively analyze the choice of screening test and evaluate the survey results by study arm. As exploratory analyses, we will evaluate response by practice location, age, gender, race/ethnicity, and income at the level of zip code.

Analysis will be conducted by blinded members of the research team at least four months after the last FIT is mailed.

## Final Statistical Analysis Plan

**\*\*New changes from initial protocol notated in bold, parts removed from initial protocol notated in strikethrough**

### Analysis Plan

#### 1.1 Power and Sample Size

Approximately 900 potentially eligible subjects will be identified via a data abstraction by Penn Data Store. Through other projects in primary care practices at Penn Medicine we found the accuracy rate of the EMR algorithm to be approximately 75%. As such, we anticipate we will have enough patients to enroll 423 subjects (and randomize 141 into each arm). We estimate a base return rate for the colonoscopy only (control) arm to be 5%, and we will consider a meaningful increase in response rate to be ~~10~~ **11** percentage points for both the sequential choice and active choice arms as compared to control. This will be sufficient sample size to detect a ~~10~~ **11** percentage point increase in response rate using a two-tailed chi-square test with 80% power and a Type 1 error rate of .025, accounting for two pairwise comparisons with Bonferroni correction ( $.05/2 = .025$ ). ~~5% level of significance.~~

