## **Statistical Considerations**

### **1.1 Power and sample size**

Approximately 900 potentially eligible subjects will be identified via a data abstraction by Penn Data Store. Through other projects in primary care practices at Penn Medicine we found the accuracy rate of the EMR algorithm to be approximately 75%. As such, we anticipate we will have enough patients to enroll 423 subjects (and randomize 141 into each arm). We estimate a base return rate for the colonoscopy only (control) arm to be 5%, and we will consider a meaningful increase in response rate to be ~~10~~ **11** percentage points for both the sequential choice and active choice arms as compared to control. This will be sufficient sample size to detect a ~~10~~ **11** percentage point increase in response rate using a two-tailed chi-square test with 80% power and a ~~5% level of significance~~. Type I error rate of .025, accounting for two pairwise comparisons with Bonferroni correction ( $.05/2 = .025$ ).

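### Holm's step-down would give more power than plain Bonferroni for the two primary comparisons, at the same 5% familywise error and the same 423 patients

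*Supplement*

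**What the plan says.** The final SAP, 1.1 Power and Sample Size, plans for a "two-tailed chi-square test with 80% power and a Type 1 error rate of .025", the level being set by "accounting for two pairwise comparisons with Bonferroni correction", that is, by halving .05. The same rule stands in the final protocol under Statistical Considerations 1.1 ("Type I error rate of .025, accounting for two pairwise comparisons with Bonferroni correction") and under Analysis Plan 1.1. The inputs are 141 subjects per arm, a 5% control rate and a meaningful increase of "11 percentage points for both the sequential choice and active choice arms as compared to control".

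The Data Analysis section (final SAP 1.2; final protocol, Statistical Considerations 1.2 and Analysis Plan 1.2) says that arms 2 and 3 are each compared with arm 1 by chi-square, by intention to treat, and that arm 2 against arm 3 is secondary. It gives no significance threshold and no multiplicity rule. No step-down or other sequential procedure appears anywhere. The Bonferroni level is found only in the power statements.

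**The concern.** With two primary hypotheses and a fixed .025 for each, a p-value between .025 and .05 in one comparison fails even when the other comparison has clearly succeeded. Holm's procedure allows the second comparison to be judged at .05 in that case, without weakening familywise control.

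The plan assumes the same benefit in both outreach arms, and this is where a step-down gains most. Power per comparison is also close to the 80% target, so power that costs no patients is worth having. At stake is a trial that shows one strategy beats colonoscopy-only outreach but narrowly fails to show the second, when a standard rule with the same error guarantee would have shown both.

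**Working it through.** **Inputs** (final SAP 1.1 and 1.2): control 5%; each intervention arm 16% (5% + 11 points); 141 per arm; two-sided .025 for each of two comparisons; one shared control arm.

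**Step 1: reproduce the stated 80%.** Normal approximation with pooled variance under the null:
- z for two-sided .025 = 2.2414; mean rate = (.05 + .16)/2 = .105
- SE0 = √(2 × .105 × .895 / 141) = .03651
- SE1 = √((.05 × .95 + .16 × .84) / 141) = .03592
- Power = Φ((.11 − 2.2414 × .03651) / .03592) = Φ(.784) = 78.4%

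With unpooled variance the result is 79.4%. Exact enumeration of all binomial outcomes, using the uncorrected chi-square, gives 80.3%. The stated figure holds.

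**Step 2: why Holm keeps the error rate.** If both null hypotheses are true, a false rejection requires the smaller p-value to be at most .025, which is the Bonferroni event, so the bound is .025 + .025 = .05. If exactly one null is true, it can be rejected only with its own p-value at most .05. Familywise error is therefore bounded by .05 in every case, whatever the correlation from the shared control.

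**Step 3: power by exact enumeration** (141 per arm, shared control, uncorrected two-sided chi-square). A comparison gains under Holm only when its own p-value lies between .025 and .05 and the other is at most .025.

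| True rates: control / arm / arm | Quantity | Bonferroni | Holm |
|---|---|---|---|
| 5 / 16 / 16% (plan) | each comparison | 80.33% | 85.03% |
| | both significant | 68.65% | 78.05% |
| | at least one | 92.01% | 92.01% |
| 5 / 15 / 15% (10-point effects) | each comparison | 73.09% | 78.35% |
| | both significant | 59.02% | 69.54% |
| 5 / 16 / 10% (assumed) | stronger arm | 80.33% | 80.93% |
| | weaker arm | 25.26% | 33.65% |
| 5 / 16 / 5% (assumed; one arm works) | effective arm | 80.33% | 80.46% |

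Check on the first block, using both = sum of the two − at least one: Bonferroni 2 × 80.33 − 92.01 = 68.65; Holm 2 × 85.03 − 92.01 = 78.05. The gain per comparison is 85.03 − 80.33 = 4.70 points, and for both it is 2 × 4.70 = 9.40 points.

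**Step 4: error rates, same method.**

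| Situation | Bonferroni | Holm |
|---|---|---|
| Both nulls true, rate 5%: any false rejection | 4.28% | 4.28% |
| Both nulls true, rate 10%: any false rejection | 4.48% | 4.48% |
| One arm ineffective (5%), other 16%: false rejection of the ineffective arm | 2.31% | 4.15% |
| Same, other arm 30% (assumed) | 2.31% | 4.81% |

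The two procedures agree when neither arm works. When exactly one works, Holm uses more of the permitted 5%.

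**The case against.** Bonferroni is valid, pre-specified and simple, it delivers the 80% it claims, and choosing between valid multiplicity methods is partly taste. All of that stands except the last part: Holm rejects everything Bonferroni rejects under the same strong guarantee, so on power alone there is no trade-off.

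There is a trade-off elsewhere. Fixed .025 tests pair directly with 97.5% confidence intervals, whereas a comparison won at Holm's .05 step may have such an interval that includes zero. The extra power also comes with a higher false-positive rate for an ineffective arm when the other arm works. Both points stand as costs to disclose. Neither breaks the 5% limit.

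A reader might infer three stronger things that the documents do not support:
- **That the trial is underpowered because the chance of showing both effects is below 80%.** The plan sets 80% per comparison and compares the arms separately. It sets no target for both, and Holm does not quite reach 80% on that measure either.
- **That the move to .025 forced the target from 10 to 11 points.** The two changes appear together at a fixed sample size, but neither the modifications log nor the summary of SAP modifications gives that reason. The proposed fix leaves the 11-point planning figure in place.
- **That the analysis section itself commits to a fixed .025.** It states no threshold. The rule is read from the power paragraphs.

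**Conclusion.** The point holds as a cheap improvement. The present rule is correct and its power claim is met. Under the plan's assumption of equal 11-point effects, Holm adds about 4.7 points of power per comparison and about 9.4 points for showing both, with no added patients. With 10-point effects in both arms the gains are about 5.3 points (78.35 − 73.09) and 10.5 points (69.54 − 59.02).

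The benefit is confined to the second comparison. It does nothing for the chance of at least one success and almost nothing if only one strategy works (80.46 − 80.33 = 0.13 point). The figures rest on 141 per arm, a 5% control rate and the uncorrected chi-square. The scenarios with unequal effects are assumptions used to show the range.

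**What to change.** In the Data Analysis section (final SAP 1.2, and the matching 1.2 paragraphs of the final protocol), add before any unblinded analysis a sentence to this effect: the p-values for arm 2 against arm 1 and arm 3 against arm 1 are judged by Holm's procedure at a familywise .05, the smaller at .025 and, only if it is significant, the other at .05. This also supplies the decision rule that the section now lacks. Keep the .025 power statement as the conservative planning figure.

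If 97.5% intervals are reported, add a footnote that a comparison declared significant at the .05 step may have an interval that includes zero. Record that the false-positive rate for a single ineffective arm rises from 2.3% to about 4.1–4.8%, within the 5% limit.

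The cost is one sentence and a footnote, with no new data, tests or patients. If unblinded results have already been seen, the switch can no longer be presented as pre-specified, and the Bonferroni level should stand.
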